## Methods/Design

### Study design

MODE is a randomized, parallel, superiority and single blinded controlled trial comparing the effectiveness of two active interventions – high frequency (*n* = 30) vs low frequency (*n* = 30) psychoanalyses – in modifying brain structure and function over one year of treatment chronic depression patients who have a history of early life trauma (Fig. 1).

**Fig. 1 Fig1:**
[figure not shown]
Flow chart of the study

This study design will overcome many of the limitations of prior psychotherapy effectiveness studies. It will include an active control condition rather than a mere wait list, thereby controlling for the effects of interpersonal attention and interaction. Randomization and statistical evaluation will be performed by independent teams. Moreover, the active comparator condition, low frequency psychoanalysis, will help to control for the “allegiance” effects that confound most psychotherapy trials [85]. Finally, comparing high vs low frequency psychoanalyses will inherently provide an assessment of dose–response effects of psychoanalytic therapy on brain structure and function. Establishing dose–response associations will further improve causal inference in our study design.

In addition to randomization of depressed patients, we will include a group of healthy control participants (*n* = 30) who are free of psychiatric illness. They will not undergo treatment and therefore will not be randomized. They will undergo similar assessments and MRI scanning at one-year intervals. Their measures will serve as reference points to help discern whether study treatments induce brain changes toward or away from normal values.

### Inclusion and exclusion criteria

#### Patients

Patients between 21 and 60 years of age of all genders suffering from chronic depression will be included in the study. Patients must be continuously depressed for more than one year and currently meet a diagnosis of major depression or dysthymia. The SCID interview will confirm a yearlong history of depression. Only patients without antidepressant (AD) medication at study onset will be included. Only patients with early trauma on at least one of the subscales of the CTQ will be included (Table 1).

**Table 1 Tab1:** Inclusion and exclusion criteria for patients

Inclusion Criteria	Exclusion Criteria
• Diagnosis of major depression and/or dysthymia (based on Structural Clinical Interview-SCID) for at least 12 months • BDI-2 > 17 • QIDS > 9 • CTQ: at least trauma at one of the subscales • Age: 21–60 years • Sufficient knowledge of local language • Informed consent to study protocol • Need to be free of anti-depressant, anti-anxiety, and antipsychotic medication for at least 3 weeks before baseline assessment and be deemed stable by their treating clinician at the study onset	• Current or past psychotic symptoms in the last 3 years, schizoaffective, schizophrenic, or bipolar affective disorder • Substance dependence current or during the last three years • Dementia • Borderline, schizotypal, or antisocial personality disorder • Acute suicidality • Reduced intellectual capacity • Serious physical illness that strongly affects the depression or is causal for the depression • Concurrent psychotherapy • Technical exclusion criteria for MRI (metallic tattoos, pacemakers, or other metal parts in the body etc., according to special guidelines of the local MRI team)

#### Healthy control participants

Inclusion criteria are: (1) no history of prior or current psychiatric diagnoses (Structured Clinical Interview for DSM-SCID); (2) no prior history of trauma on any of the CTQ subscales; (3) 21–60 years of age; and (4) sufficient knowledge of the local language to undergo assessments. Exclusion criteria are: (1) serious physical illness; and (2) any current psychotherapeutic or psychotropic treatment. Healthy controls will be group-matched on age and gender to participants in the treatment groups (Table 2).

**Table 2 Tab2:** Inclusion and exclusion criteria for healthy participants

Inclusion Criteria	Exclusion Criteria
• No history of prior or current psychiatric diagnoses (based on Structural Clinical Interview-SCID) • CTQ: No prior history of trauma on any of the subscales • Age: 21–60 years • Sufficient knowledge of local language • Informed consent to study protocol	• Serious physical illness that strongly affects the depression or is causal for the depression • Concurrent psychotherapy • Technical exclusion criteria for MRI (metallic tattoos, pacemakers, or other metal parts in the body etc., according to special guidelines of the local MRI team)

#### All participants

Standard MRI exclusion criteria will apply (metallic tattoos, pacemakers, or other metallic implants).

### Intervention and comparator

Study intervention will be comprised of low frequency psychoanalytic psychotherapy (1 session a week) for early traumatized, chronically depressed patients and high frequency psychoanalytic psychotherapy (3–4 weekly sessions). The active comparator condition, low frequency psychoanalysis, delivered by study therapists who are experts in delivering both frequencies, and with the same overall manual based theoretical framework and technical interventions [86], will ensure that they will be equally aligned to both high and low frequency therapies. A group of healthy controls will be needed for brain imaging comparison purposes. A control group will allow to measure cortical thickness in patients with chronic depression in comparison to healthy control participants. Therapy sessions (45–50’ each) will be delivered in the private practice rooms or rooms of the outpatient clinics of the local psychotherapeutic institutions. Patients who will require a combination therapy of medication and psychotherapy during treatment will not be excluded but form a special subgroup that will be treated separately during data analyses. Patients who will require a change in psychotherapy setting during treatment according to patient and therapist decision will be analyzed as randomized. MODE study duration will be one year, but after 1 year of treatment initiation, treatment may continue according to patient and therapist decision. Treatments will be financed in the usual way in the participating countries (in Germany by the health insurance companies, in the US and Switzerland partly by the health insurance companies, partly by the patients themselves).

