### Data analysis

Analyses will follow an intent-to-treat strategy comparing patients in the groups to which they were originally randomized.

All data will be scored and rescored by separate staff members and checked for accuracy prior to double entry into a REDCap database. Before conducting inferential statistics, we will explore data using descriptive analyses, data visualization, and examining the distributions of all imaging and clinical data. When necessary for continuous variables used as dependent variables, appropriate transformations to obtain approximate normality will be performed.

We will test a priori Primary Hypotheses in the 60 depressed participants by assessing a treatment-by-time interaction in multiple general linear models with repeated measures analyses in an intent-to-treat analysis applied to our various brain measures as dependent variables, including cortical thickness, task-based fMRI activation, resting state connectivity, and FA & ADC measures. Treatment (high vs low frequency) will be the independent variable. When testing hypotheses, we will account appropriately for the correlation of repeated measures across the two time points of measurement (baseline and 1 year) and the spatial correlation within each of our imaging measures. Covariates will include age and sex of the participants. We will examine parameter estimates and 95% confidence intervals, approximate the p-values of component terms, and estimate effect sizes in our final models. Least squares estimates (or maximum likelihood estimates) and their standard errors will be calculated for all models and plotted to assist in interpretation of significant main effects and their interactions. We will ensure that overall, study-wide Type I error-rate is maintained, correcting for multiple comparisons using False Discovery Rate (FDR). FDR-corrected *p*-values < 0.05 will be color-coded and displayed on a template brain.

The 30 healthy controls will be used to estimate the mean and variance of brain measures in the healthy population quantify the effects of high and low frequency psychoanalysis on brain measures and to aid their interpretation as either normalizing a previously abnormal brain measure or introducing a new brain difference that attenuates symptoms.

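### The rule that patients who start medication are handled separately in the analysis conflicts with the intent-to-treat comparison of all 60 patients, and nothing says which governs the primary test

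*Protocol article*

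**What the plan says.** Three parts of the protocol article bear on this.

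- **Entry.** The eligibility text for patients states: "Only patients without antidepressant (AD) medication at study onset will be included". Table 1 adds: "Need to be free of anti-depressant, anti-anxiety, and antipsychotic medication for at least 3 weeks before baseline assessment".
- **Events during treatment.** Under Intervention and comparator, patients who come to need medication alongside psychotherapy "will not be excluded but form a special subgroup that will be treated separately during data analyses". The next sentence covers a different event: "Patients who will require a change in psychotherapy setting during treatment according to patient and therapist decision will be analyzed as randomized".
- **Analysis.** The Data analysis section opens: "Analyses will follow an intent-to-treat strategy comparing patients in the groups to which they were originally randomized". It continues: "We will test a priori Primary Hypotheses in the 60 depressed participants by assessing a treatment-by-time interaction". On adjustment it says: "Covariates will include age and sex of the participants". The design is "high frequency (*n* = 30) vs low frequency (*n* = 30) psychoanalyses".

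The Missing data section covers missed visits, dropout and unusable scans. It does not mention medication start. Table 3 records medication at visits 1 to 5.

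**The concern.** Patients enter without these drugs, so needing one during the year arises after allocation and may depend on the allocated session frequency. An arm comparison that leaves out patients because of such an event no longer compares the randomised groups. The protocol rests its causal claims about brain change on randomisation, so this matters to its main purpose.

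The protocol also handles two neighbouring post-randomisation events differently. A change of psychotherapy setting leaves the patient in the randomised arm, while a medication start moves the patient to a separate subgroup. Read together, the two sentences suggest that medicated patients are not to be analysed as randomised. The Data analysis section says that everyone is.

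Three things are at stake: possible bias in the high-versus-low frequency effect on the MRI measures and on secondary outcomes such as the BDI-II, loss of power in a trial of 60 patients, and an analyst's freedom to choose between the two rules after seeing the data.

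**Working it through.** **1. The passages side by side.** The Data analysis section puts all 60 patients, in their randomised arms, into the primary treatment-by-time test. Intervention and comparator puts an unspecified number of those same patients into a subgroup handled apart. Both cannot hold for the same test. Nothing bridges them: the named covariates are age and sex, with no medication term, and no text assigns the separate handling to a secondary or sensitivity analysis.

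**2. Bias if medicated patients leave the arm comparison.** The documents give no rate of medication start, no expected difference between arms and no link between medication start and outcome, so these are assumptions. Suppose there is no true effect, the outcome is standard normal (higher is better), a fraction q with the worst prognosis starts medication, and prognosis correlates r with outcome. The mean of those who remain is r × φ(z_q)/(1 − q).

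- q = 0.10: 0.1755/0.90 = 0.195
- q = 0.15: 0.2332/0.85 = 0.274
- q = 0.30: 0.3477/0.70 = 0.497

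The shift in high minus low is r times the difference between arms:

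| High vs low medicated | r = 0.3 | r = 0.5 | r = 0.7 | r = 1 (perfect selection) |
|---|---|---|---|---|
| 20% vs 20% | 0 | 0 | 0 | 0 |
| 15% vs 30% | −0.07 | −0.11 | −0.16 | −0.22 |
| 10% vs 30% | −0.09 | −0.15 | −0.21 | −0.30 |

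For 10% vs 30%, a simulation gave the same shifts at r = 0.3, 0.5 and 0.7, with type I error of 6.1%, 8.1% and 11.2% against a nominal 5%. With equal 20% rates it stayed at 5%. Reversing the assumed rates reverses the sign.

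**3. Power.** The Power calculation section states 80% for d = 0.5, α = 0.05 and 30 per arm. As a two-arm, two-sided comparison in plain SD units, power is Φ(0.5/√(2/30) − 1.96) = Φ(1.936 − 1.960) = 49%, so the stated figure is not reproduced on that basis. It would need a baseline-to-one-year correlation of about 0.76 (change score) or 0.72 (baseline-adjusted), and the article gives none. That is a separate matter, so both starting points are shown. For the 80% basis, the standardised effect giving 80% at 30 vs 30 is (1.960 + 0.842) × √(2/30) = 0.723.

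| Patients left (assumed) | From the stated 80% | From 49% (plain d = 0.5) |
|---|---|---|
| 30 vs 30 | 80% | 49% |
| 27 vs 27 (10% each) | 76% | 45% |
| 24 vs 24 (20% each) | 71% | 41% |
| 21 vs 21 (30% each) | 65% | 37% |
| 27 vs 21 (10% vs 30%) | 70% | 40.5% |

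Worked case, 24 vs 24: Φ(0.723/√(2/24) − 1.96) = Φ(2.506 − 1.960) = Φ(0.546) = 71%. At 20% per arm the separated subgroup would hold 6 vs 6 patients, too few to support a comparison of its own.

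**The case against.** The sentence on medication never mentions the primary analysis and says that these patients are kept, not excluded. The section that defines the primary test names all 60 patients and intent-to-treat, and the abstract repeats intent-to-treat. The separate handling can therefore be read as an extra subgroup analysis beside a complete primary test. There is a visible reason for one: the cortical-thickness and default-mode hypotheses draw on medication-versus-placebo trials, so the protocol itself treats drugs as able to change these measures.

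This stands in part. A reader might infer that the protocol definitely removes medicated patients from the primary comparison. The documents do not support that as fact. It is the more natural reading of the medication sentence, given its contrast with the next one, but the Data analysis section points the other way. What remains is that no text confines the separate handling to a supplementary role.

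The objection to the size also stands. A reader might infer a bias of 0.22 SD against high frequency. That figure needs 15% vs 30% medicated and perfect selection of the worst responders. The documents do not say that once-weekly patients would be medicated more often, or how closely medication start, presumably prompted by symptoms, tracks the MRI measures.

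**Conclusion.** The point holds as an unreconciled conflict between two stated rules. If the medication rule governs the primary test, that test is conditioned on a post-randomisation event.

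Neither the direction nor the size of any bias can be derived from the documents. It is about zero with equal rates and equal selection in both arms. It is about 0.1 to 0.2 SD under assumed rates of 10–15% vs 30% and correlations of 0.3 to 0.7, which is not trivial beside a design effect of d = 0.5. Power falls whenever patients are set aside, even without bias: at 20% per arm, from the stated 80% to about 71%, or from about 49% to 41% in plain SD units. If the Data analysis section governs and the subgroup analysis is only additional, the primary test has neither problem. The protocol should say so before data are seen.

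**What to change.** Reconcile the two sections in one place:

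- Under Intervention and comparator, replace the separate-handling wording with a statement that all randomised patients stay in their allocated arm in the primary analysis, whatever medication they start. This matches the Data analysis section and the existing rule for changes of psychotherapy setting.
- Report medication start by arm.
- Label any analysis that separates, removes or models medicated patients as supplementary or sensitivity. This keeps the mechanistic question open without letting it decide who is in the primary test.

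The cost is a sentence or two here, carried into the statistical analysis plan. No new data are needed, because Table 3 already records medication at visits 1 to 5, and clinical management is untouched. The one small downside is that the primary estimate will include any effect of added medication, which the labelled sensitivity analysis can examine.

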### Outcome measures

Study participants will be assessed as detailed below and in Table 3, for primary and secondary outcome measures. Patients will be assessed by independent and trained clinicians who are blind to treatment conditions.

**Table 3 Tab3:** Study timetable of assessments

Assessments	Screening	Visit 1	Visit 2	Visit 3	Visit 4	Visit 5
*Description*	*Inclusion*	*Study start*	*FU 3 months*	*FU 6 months*	*FU 9 months*	*Study end*
*Days*	*Day -x*	*Day 0*	*Day 91*	*Day 182*	*Day 273*	*Day 365*
*Window (dates)*			± *7*	± *7*	± *7*	± *3*
*Weeks*		*0*	*13*	*26*	*39*	*52*
Informed consent signed	X					
Eligibility	X					
Demographics		X				
SCID (CI)	X	(X)^a^				X
Psychoanalytic interview	X	(X)^a^				
MRI scan	X	(X)^a^				X
Trust game	X	(X)^a^				X
GAF (Cl)		X				X
BDI-II (SR)	X	X	X	X	X	X
DEQ (SR)		X	X	X	X	X
QIDS (Cl, SR)		X	X (only SR)	X (only SR)	X (only SR)	X
SCL-90-R (SR)		X	X	X	X	X
CTQ (SR)	X					
IIP (SR)		X	X	X	X	X
Work Ability Index (SR)		X	X	X	X	X
OPD_SF (SR)		X	X	X	X	X
Dream Diary (SR)						X
Patient trauma narratives		X				X
WAI-SRp (SR)		Collected each month from Assessment 1 to 5				
Psychotherapy		Throughout study				
Adverse Events			X	X	X	X
SAE		Throughout study				
Medication		X	X	X	X	X

*FU* Follow-up, *Cl* Clinician rated, *SR* Self-reported, *SCID* Structured Clinical Interview for DSM, *GAF* Global Assessment of functioning, *BDI-II* Beck Depression Inventory-II, *DEQ* Depressive Experience Questionnaire, *QIDS* Quick Inventory of Depressive Symptoms (Cl, SR), *SCL-90-R* Symptom Checklist, *CTQ* Childhood Trauma Questionnaire, *IIP* Inventory Interpersonal Problems, *WAI* Work Ability Index, *OPD-SF* OPD structure questionnaire, *WAI-SRp* Working Alliance Inventory, *SAE* Severe Adverse Event

^a^Depending on the availability of the persons concerned, the first MRI examination, the administration of the Trustgame, the SCID interview, and the psychoanalytical interview can take place at the screening visit or visit 1

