**Methods/design:**

Patients with chronic major depression and a history of early life trauma will be recruited, assessed, and treated across 3 international sites: Germany, Switzerland, and the United States. They will be randomized to one of two treatment arms: either (1) once weekly psychoanalytic psychotherapies, or (2) 3–4 times weekly psychoanalytic psychotherapies. They will have full clinical characterization as well as undergo MRI scanning at study baseline prior to randomization and again one year later. A group of matched healthy controls will undergo similar assessments and MRI scanning at the same time points to help discern whether study treatments induce brain changes toward or away from normal values. Primary study outcomes will include anatomical MRI, functional MRI, and Diffusion Tensor Imaging measures. Study hypotheses will be tested using the treatment-by-time interaction assessed in multiple general linear models with repeated measures analyses in an intent-to-treat analysis.

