###### Dream diary

Dreams will be collected in dream diaries ideally at each follow-up points and latest at study termination with the intent to examine dream characteristics in participants with chronic depression and early trauma. Participants can write freely about their dreams. To help participants document their dreams, an exemplary table will be provided where they can write a description of their dream(s) and report on the feelings they experienced in the dream(s) as well as elements of real life associated to the dream(s). Dream characteristics and changes of the manifest content of dreams as reported in the dream diaries will be assessed using the Social Cognition and Object Relations Scale-Global Rating Method (SCORS-G**;** [107]) as well as the LIWC (see above).

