### Randomization

The randomization procedure will consist of a computer-generated sequence of random numbers using SPSS (SPSS Statistics, version 28), which will then be used to allocate patients to either of the 2 treatment arms. The randomization sequence will be generated and maintained by an independent study administrator in Frankfurt. Once the patient is included the ID number is communicated to the study administration in Frankfurt. On the same day, the randomization arm will be communicated to the local team and applied to the participant included.

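### Table 3 and the Randomization section do not secure the abstract's order of baseline before randomisation, and the QIDS entry criterion is not scheduled at the visit where eligibility is marked

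*Protocol article*

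**What the plan says.** The abstract (Methods/design) gives the intended order: "They will have full clinical characterization as well as undergo MRI scanning at study baseline prior to randomization and again one year later".

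The Randomization section gives the trigger: "Once the patient is included the ID number is communicated to the study administration in Frankfurt". It continues: "On the same day, the randomization arm will be communicated to the local team and applied to the participant included".

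Table 3 (Outcome measures) labels the Screening column *Inclusion* (Day -x) and marks Eligibility only there. Visit 1 is labelled *Study start* (Day 0). The table has no randomisation row. Its footnote a reads, after a condition on availability, "first MRI examination, the administration of the Trustgame, the SCID interview, and the psychoanalytical interview can take place at the screening visit or visit 1".

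Table 1 lists among the entry criteria "Diagnosis of major depression and/or dysthymia (based on Structural Clinical Interview-SCID) for at least 12 months" and "BDI-2 > 17 • QIDS > 9 • CTQ: at least trauma at one of the subscales".

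The secondary hypothesis on psychopathology expects greater improvement in manifest dreams under high frequency treatment, measured with DREAMS-C. The Dream diary section collects diaries "ideally at each follow-up points and latest at study termination" and scores them with SCORS-G and LIWC. Table 3 marks the diary only at Visit 5.

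**The concern.** The primary analysis is a treatment-by-time interaction on two time points, baseline and one year. It is protected by randomisation only if baseline is measured before anyone can react to the allocation. Patients cannot be blinded to whether they attend once or three to four times a week. If the arm is issued at inclusion and the baseline is taken at the next visit, two things can go wrong. Responses can already differ by arm, and patients disappointed with their arm can leave before the first scan.

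Eligibility raises a second problem. If a criterion is measured after the arm has been issued, a patient who fails it must either be excluded after randomisation, contrary to the intent-to-treat strategy in the Data analysis section, or be kept although ineligible.

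For dreams, a hypothesis of improvement needs a starting value and an agreed scale.

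**Working it through.** The core question is the order of events, so the check is mainly a comparison of the texts.

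**Step 1. When each baseline is first scheduled (Table 3).**

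| Item | Screening (*Inclusion*) | Visit 1 (*Study start*) |
|---|---|---|
| Eligibility, CTQ | yes | no |
| BDI-II | yes | yes |
| MRI, Trust game, SCID, psychoanalytic interview | yes | allowed instead (footnote a) |
| QIDS, GAF, DEQ, SCL-90-R, IIP, Work Ability Index, OPD-SF, trauma narrative | no | first mark |

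If inclusion in the Randomization section means the column labelled *Inclusion*, the order is: Screening, arm issued the same day, then Visit 1. The third row can then follow disclosure and the fourth row would do so. BDI-II and CTQ are not exposed, because both have a Screening value. If instead a patient counts as included only once the Visit 1 assessments are done, all baselines precede the arm. No sentence outside the abstract settles which applies.

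**Step 2. Eligibility.** The BDI-2 and CTQ criteria can be checked at Screening. QIDS > 9 cannot, because no QIDS is scheduled there. The SCID, which must confirm the year-long history, may not have been done. This misfit with the single Eligibility mark exists on either reading of Step 1. It leads to post-randomisation exclusions, or to retained ineligible patients, if the ID is sent off on the strength of the Screening mark.

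**Step 3. How a late baseline would act on the primary contrast.** With two time points, the interaction is the difference in mean change:

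(one year − baseline) in high frequency, minus (one year − baseline) in low frequency.

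Let f be the fraction of patients whose baseline follows disclosure, taken as equal in both arms. Let Δ be the difference between arms in the mean shift that disclosure causes, in SD units. The contrast then moves by f × Δ in absolute size. A shift common to both arms cancels.

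The article gives neither f nor Δ. The values below are assumptions for scale only, set against the planning effect d = 0.5 in the Power calculation section and treating both as being on the same SD scale:

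- f = 1, Δ = 0.1 to 0.3: movement 0.1 to 0.3 SD, which is 0.1/0.5 = 20% to 0.3/0.5 = 60% of d.
- f = 0.1, Δ = 0.1: 0.1 × 0.1 = 0.01 SD, which is 2% of d.
- f = 0.5, Δ = 0.3: 0.5 × 0.3 = 0.15 SD, which is 30% of d.

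The first line is a ceiling for items that all patients would have late. For the MRI, where deferral is optional, f is below 1 if any patient is scanned at Screening.

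**Step 4. Dreams.** The hypothesis names DREAMS-C. Neither the Dream diary section nor Table 8 lists it; both name SCORS-G. Neither Table 3 nor the diary text places a diary before treatment, so change from a pre-treatment value cannot be computed.

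**The case against.** The strongest reply is that the late baseline is inferred rather than stated. It depends on equating a column label with the word used in the Randomization section. The only text that orders baseline and randomisation is the abstract, and it puts baseline first. The Patients section ties inclusion to the absence of antidepressants at study onset, and Visit 1 is the study start. A patient without a SCID or QIDS does not yet meet Table 1 and so, arguably, is not yet included. On that view inclusion closes at Visit 1 and randomisation follows.

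This reply stands in part. A reader might infer that all Visit 1 baselines follow disclosure of the arm; the documents do not establish that. Nor do they establish the other order. The Eligibility mark stays at Screening. The consent section moves from consent to randomisation with no baseline step between. The Intervention and comparator section counts the study year from about the start of treatment, and Table 3 ends at Day 365, so the arm plausibly has to be known by about Day 0.

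A reader might also infer a demonstrated bias of 20 to 60% of the planning effect in the primary outcomes. That is not supported. The shift is assumed, it must differ between arms, and for MRI it shrinks with the fraction deferred. Learning one's session frequency is an unlikely cause of change in cortical thickness or DTI. It is more plausible for self-reports, the Trust game and the Cyberball task. Blinding of interviewers and the MRI team limits rater bias, but not patients' own reactions or selective loss before a deferred scan.

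On dreams, it is fair to say that change across follow-up diaries might be available, and that the arms could be compared at one year without a baseline. Only change from pre-treatment is lost. This is a secondary-outcome matter, separate from the order of randomisation.

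**Conclusion.** The concern holds as a failure to secure the stated order, not as proof that the order is broken. Table 3 and the Randomization section, read on their own labels, allow the first MRI, Trust game and SCID, and the scales first scheduled at Visit 1, to come after the arm is known.

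The eligibility finding does not depend on that reading: the QIDS criterion is unscheduled, and the SCID possibly outstanding, at the only visit marked for eligibility. The dream finding is also independent of it: the scale is named inconsistently and no pre-treatment value is planned.

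The size of any bias cannot be derived from the article. The figures under Step 3 rest wholly on assumed shifts and assumed deferral fractions. The case for repair is that baseline is one of only two time points in the primary test, there are 30 patients per arm, and the correction is cheap.

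**What to change.** - In the Randomization section, state that the patient's ID is sent for randomisation only after eligibility, including SCID and QIDS, is confirmed and all baseline assessments are complete, and that the arm is disclosed only after that.
- Add a randomisation row to Table 3 after these steps.
- Schedule the QIDS at the visit where eligibility is decided.
- Limit footnote a to timing before randomisation.
- Add a dream diary before the first therapy session, and name one dream scale consistently in the hypothesis, the Dream diary section and Table 8.
- For patients already enrolled, flag every baseline dated after disclosure of the arm. Keep the full intent-to-treat analysis as primary. An analysis without the flagged patients selects on a feature arising after randomisation and reduces a sample of 60, so it can be supportive only.

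The cost is a schedule amendment, randomisation a few days later for some patients, and one short extra diary entry. If practice already follows the abstract, one clarifying sentence settles the order; the QIDS and dream items still need correcting.
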